## Abstract

**Background:**

Fecal occult blood test screening in Canada is sub-optimal. Family physicians play a central role in screening and are limited by the time constraints of clinical practice. Patients face multiple barriers that further reduce completion rates. Tools that support family physicians in providing their patients with colorectal cancer information and that support uptake may prove useful. The primary objective of the study is to evaluate the efficacy of a patient decision aid (nurse-managed telephone support line and/or colorectal cancer screening website) distributed by community-based family physicians, in improving colorectal cancer screening rates. Secondary objectives include evaluation of (dis)incentives to patient FOBT uptake and internet use among 50 to 74 year old males and females for health-related questions. Challenges faced by family physicians in engaging in collaborative partnerships with primary healthcare researchers will be documented.

**Methods/design:**

A pragmatic, two-arm, randomized cluster controlled trial conducted in 22 community-based family practice clinics (36 clusters) with 76 fee-for-service family physicians in Winnipeg, Manitoba, Canada. Each physician will enroll 30 patients attending their periodic health examination and at average risk for colorectal cancer. All physicians will follow their standard clinical practice for screening. Intervention group physicians will provide a fridge magnet to each patient that contains information facilitating access to the study-specific colorectal cancer screening decision aids (telephone help-line and website). The primary endpoint is patient fecal occult blood test completion rate after four months (intention to treat model). Multi-level analysis will include clinic, physician and patient level variables. Patient Personal Health Identification Numbers will be collected from those providing consent to facilitate analysis of repeat screening behavior. Secondary outcome data will be obtained through the Clinic Characterization Form, Patient Tracking Form, In-Clinic Patient Survey, Post-Study Follow-Up Patient Survey, and Family Physician Survey. Study protocol approved by The University of Manitoba Health Research Ethics Board.

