## Methods/design

### Setting and participants

Family physicians will be recruited over a six month period from seven community areas (Figure 1) within the city of Winnipeg, Manitoba, Canada. Winnipeg is the capital city of the province with a population of approximately 685,000 (half the population of the province). In order to be eligible for the study, FPs must be in regular family practice (full or part-time), fee-for-service, solo or group practice and may be a member of the Physician Integrated Network and/or Uniting Primary Care and Oncology Network (Table 1). Once a family physician/medical clinic has agreed to participate in the study, a Family Physician/Clinic Characterization Form (Additional file 2) will be completed to document the routine care provided by each family physician in regards to CRC screening practices with the FOBT, whether they utilized an electronic medical record, have an on-site laboratory, and to document any additional information necessary to ensure minimal intrusiveness of the study protocol in the daily functioning of the clinical practice. Each family physician will enroll 30–35 patients who are: (1) attending their periodic health exam; (2) considered at average risk of developing colorectal cancer (Table 2); and (3) provide informed consent to participate. A patient tracking form (Additional file 3) will be filled out by the family physician for each patient enrolled.

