### Sample size determination, randomization, and statistical analysis

Individual randomization of physicians within a group-practice and individual patients to either the control or intervention arm of the study is not feasible [32]. A cluster randomized design was chosen in which family physicians within a group practice were randomized to the same experimental group (control or intervention) and considered a cluster. Randomization of clusters will be conducted by a biostatistician using a computer-generated list and all of a physician’s patients will receive the same experimental treatment (control or intervention). Our protocol defines a multi-level analysis facilitating analysis of the intraclass correlation coefficient (ICC) for each primary group-level outcome (patients, FP, clinics/clusters) [32]. To ensure an even distribution of cluster-level characteristics between experimental groups, clusters will be randomized within strata based on membership in the Physician Integrated Network (PIN) and/or Uniting Primary Care Oncology Network (UPCON) [28]. These represent two quality improvement initiatives in Manitoba (Table 2). Clusters will be block randomized based on the number of collaborating FPs within a practice. An absolute increase in FOBT screening rates of 15% from the current 42% in Manitoba will be considered clinically significant [14]. Sample size was determined by a biostatistician using PASS (Power and Sample Size, 2002) software and a computer simulated ICC value of 0.6 [33] taking into consideration the clustered design of the trial [34]. This is a very conservative estimate of the minimum detectable effect size (MDEF) given the proposed sample size. Based on logistic regression a cluster size of 41 clusters each enrolling 30 to 35 patients (of which 80% are in the group that does not utilize the supplied intervention/magnet and 20% are in the group that does utilize the intervention/magnet; 1230 observations) will achieve 90% power at a 0.05 significance level to detect a change from the baseline value of 0.400 to 0.550 and corresponds to an odds ratio of 1.833. In the event that family physician collaboration/retention and/or patient recruitment proves to be more difficult than anticipated, a logistic regression with a cluster size of 28 (840 observations) achieves 80% power with the same outcomes.

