Research has shown a majority of patients completing the FOBT do so within 4 to 6 weeks [20]. In order to allow adequate time to complete the FOBT and return it to the laboratory, patients will be given four months to do so. Those patients not returning their FOBT test within a period of four months will be scored as failing to complete the FOBT test.

Analysis of results will be based on the intention to treat (ITT) model. All Statistical analysis will be performed using SAS 9.2 ® software. Categorical variables will be compared using the Chi-square test. The time taken to return FOBT cards will be analyzed with Cox’ Proportional Hazards Regression analysis. Due to the clustered design, study outcomes will be measured at the level of the patient, family physician, and medical clinic/cluster. The analysis will utilize multi-level logistic regression that accounts for variance among patients with the same FP, FP within the same cluster, and among the clusters. The SAS® GLIMMIX procedure will be used to model patient FOBT completion rate (response variable). This will enable evaluation of the rate of patient FOBT compliance within medical clusters and individual FPs. Sources of variance included in the model will include cluster level (treatment, electronic medical record or paper charts, PIN and/or UPCON membership), family physician level (gender, solo/group practice), and patient level (age, gender, socioeconomic status, and previous FOBT screening history) variables as well as random variation.

A computerized randomization number list will be used to select 10 patients per FP to be contacted for a Post-Study Follow-Up Survey (Additional files 4 and 5) conducted by telephone. Only those patients providing permission to be contacted will be included. Those patients surveyed will be asked for permission to document their Personal Health Identification Number which will facilitate future studies conditional to Health Research Ethics Board (HREB) approval of analysis of repeat colorectal cancer screening behavior over time.

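### Clinic and cluster are treated as one level, yet 22 clinics give 36 clusters, and the stated variance structure has no clinic level distinct from the cluster

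*Protocol article*

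**What the plan says.** The Abstract (Methods/design) gives the size of the trial as "conducted in 22 community-based family practice clinics (36 clusters) with 76 fee-for-service family physicians" and describes the analysis in these terms: "Multi-level analysis will include clinic, physician and patient level variables".

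The section on sample size, randomization and statistical analysis sets the unit of allocation: "family physicians within a group practice were randomized to the same experimental group (control or intervention) and considered a cluster". Allocation is stratified by network membership, and "Clusters will be block randomized based on the number of collaborating FPs within a practice".

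The same section runs clinic and cluster together twice. The intraclass correlation is to be analysed for "each primary group-level outcome (patients, FP, clinics/clusters", and "study outcomes will be measured at the level of the patient, family physician, and medical clinic/cluster". The multi-level logistic model is then described as one that "accounts for variance among patients with the same FP, FP within the same cluster, and among the clusters". Treatment, type of medical record and network membership all enter as cluster-level variables.

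Under Setting and participants, eligible physicians may be in "fee-for-service, solo or group practice and may be a member of the Physician Integrated Network" or another named network.

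**The concern.** If clinic and cluster are one level, as the analysis text has it, 22 clinics should give 22 clusters. The article reports 36. Some clinics therefore hold several clusters, and nothing in the article explains how, or whether those clusters had to be in the same arm.

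This matters because the unit of randomization is the basis of inference in a cluster trial. Clusters in one clinic plausibly resemble each other: they may share premises, support staff, record system and network membership. The stated model has nothing above the cluster to carry that resemblance. Depending on how the clusters were allocated, the result is either a standard error that is too small, or a valid but less precise comparison in which one set of clinic staff may be running both arms.

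**Working it through.** **Inputs from the document.** 22 clinics and 36 clusters (Abstract); a cluster is the physicians of one group practice; variance levels are patient within physician, physician within cluster, and among clusters (sample size and analysis section).

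**Step 1: can 36 be derived from the text?** If clinic and cluster are the same, the count is 22, and 36 − 22 = 14 clusters are unexplained. If clusters nest in clinics, some clinics hold more than one.

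**Step 2: how many clusters share a clinic?** Let k clinics hold more than one cluster. The other 22 − k hold exactly one. Clusters that share a clinic number 36 − (22 − k) = 14 + k. Each of the k clinics holds at least two, so 14 + k ≥ 2k and k runs from 1 to 14.

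- k = 1: 15 clusters (15/36 = 42%)
- k = 14: 28 clusters (28/36 = 78%)

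**Step 3: same-clinic clusters allocated together.** Assume equal-sized clusters, and let ρ be the share of between-cluster variance that sits at clinic level. Neither is given in the document. With mᵢ clusters in clinic i, the true variance of the treatment contrast relative to the variance under independent clusters is

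1 + ρ(Σmᵢ²/36 − 1).

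Take the most even layout, 14 clinics of two clusters and 8 of one: Σmᵢ² = 14 × 4 + 8 × 1 = 64, and 64/36 = 1.78. Nominal 5% tests then have type I error 2[1 − Φ(1.96/√ratio)]:

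| ρ (assumed) | variance ratio | √ratio | type I error, normal approximation |
|---|---|---|---|
| 0.5 | 1 + 0.5 × 0.78 = 1.39 | 1.18 | 9.6% |
| 1.0 | 1.78 | 1.33 | 14.2% |

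Simulating cluster-level t-tests in this layout gave about 10% (ρ = 0.5) and 15% (ρ = 1).

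**Step 4: clusters allocated independently, 18 per arm.** In the same layout, simulated type I error was about 5% at every ρ tried. Treatment is not tied to clinic, so same-clinic clusters that land in the same arm are offset by those that land in different arms. Two other effects remain:

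- *Precision.* Weighting the cluster means by the true clinic correlation, instead of ignoring it, lowers the variance of the treatment effect by about 7% at ρ = 0.3 and about 40% at ρ = 0.7 (assumed values).
- *Mixed clinics.* A pair of same-clinic clusters falls in different arms with probability 18/35, so about 14 × 18/35 = 7.2 of the 14 two-cluster clinics would hold both arms. Strata and blocks are ignored here.

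**The case against.** The strongest reply has four parts.

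*The definition may be sound.* Solo and group practices are both eligible. A clinic that houses several practices would yield several clusters without breaking the definition. A reader might infer that clinics were deliberately split, but the document does not say so. This stands. It does not remove the problem, because such clusters would still share a clinic with no level above them.

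*Independent allocation keeps the test valid.* The text speaks of randomizing clusters and of variance among clusters. Read literally, that gives the correct type I error, as Step 4 shows. This also stands, and it is why inflated type I error is only one branch of the conclusion.

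*Spill-over is limited.* Each magnet carries a patient-specific number, which callers give to the nurse and enter to reach the website. Control patients in a mixed clinic would have no such number. A reader might infer that magnets leak across arms, or that clustering was chosen to prevent contamination. The document supports neither: its stated reason is that individual randomization was not feasible. What remains is that support staff hand out the survey that doubles as the consent form and record who declines, so staff in a mixed clinic could be working in both arms.

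*A journal article condenses, and it does name a clinic level.* Exact random effects are often left to the full plan, and record type and network membership may absorb some clinic variation. But this article itself states the unit, both counts and the variance structure, and they do not fit together. The clinic level that it names is the cluster under another label.

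**Conclusion.** The concern holds as an inconsistency with a practical consequence. Clinic and cluster are written as one level, yet the counts differ by 14, so 15 to 28 clusters share a clinic with another and are modelled as if independent. That follows from the document's own numbers, given that clusters nest in clinics.

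The statistical cost is conditional. With whole-clinic allocation, type I error is about 10 to 15% in the illustrative layout if half or all of the between-cluster variance is at clinic level. With independent allocation it is about 5%, with avoidable loss of precision and possibly mixed clinics. Both branches rest on equal-sized clusters, an assumed layout and assumed correlations.

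A reader might be tempted to take 36/22 = 1.64 as the largest possible variance understatement, with a type I error of about 12.5%. The document does not support that. With equal-sized clusters, all variance at clinic level and whole clinics in one arm, even the most even layout gives 1.78, and one clinic of 15 clusters with 21 of one gives (225 + 21)/36 = 6.83. With less variance at clinic level the ratio falls. So 1.64 is not an upper bound, and whole-clinic allocation is nowhere stated.

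**What to change.** 1. Reword the cluster definition in the sample size and randomization section so that 36 clusters in 22 clinics follow from it, and state whether clusters of one clinic could be allocated to different arms.
2. Add a random intercept for clinic above cluster in the GLIMMIX model: patient within physician, within cluster, within clinic. It protects the standard error if same-clinic clusters share an arm and recovers precision if they do not.
3. Report how many clinics hold both arms, with a sensitivity analysis that leaves those clinics out.

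The cost is a few sentences, one variance component and one extra analysis. With 22 clinics, 8 to 21 of which hold a single cluster, the clinic component may be poorly estimated, and confidence intervals may widen. The allocation itself need not change.

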**Discussion:**

The study intervention has the potential to increase patient fecal occult blood test uptake, decrease colorectal cancer mortality and morbidity, and improve the health of Manitobans. If utilization of the website and/or telephone support line result in clinically significant increases in colorectal cancer screening uptake, changes in screening at the policy- and system-level may be warranted.

**Trial registration:**

Clinical trials.gov identifier NCT01026753

## Background

The CIHR/CancerCare Manitoba Team in Primary Care Oncology Research is based in Winnipeg, Manitoba, Canada and is one of five Canadian Institutes of Health Research (CIHR) Primary Care Oncology New Emerging Team (PCO-NET) grant recipients (Additional file 1). The focus of our research is to investigate ways of supporting community-based family physicians in providing colorectal cancer services throughout the care continuum. We are a multi-disciplinary team of stakeholders and knowledge users including primary healthcare researchers, practitioners, policy and decision makers, and patients. The purpose of this team is to develop research initiatives that support evidence-based primary care oncology clinical practice, thus providing access to high quality cancer care.

Each week, approximately 430 Canadians will be diagnosed with colorectal cancer (CRC) and 175 will die of the disease, making it the second leading cause of cancer related death in Canada [1]. In Manitoba, CRC is the third most commonly diagnosed cancer (with an estimated 810 new cases in 2011) and the second leading cause of death from cancer in men and women combined (with an estimated 320 deaths in 2011) [1]. Colorectal cancer (CRC) screening rates for average risk individuals are sub-optimal in across Canada and in Manitoba [2]. Self-reported data from Manitobans indicates that approximately 38% of eligible individuals have completed an FOBT in the past two years [3]. This figure is close to that reported by Statistics Canada (2009) indicating FOBT screening rates for Manitobans of 41.9% [1]. Increased screening would reduce the physical, emotional and economic burden of CRC. It has been estimated that if approximately 70% of Canadians aged 50 to 74 completed an FOBT every two years, followed up by colonoscopy for positive FOBTs, the CRC mortality rate could be reduced by 17% [4-6].

Ninety three percent of all cases of CRC occur in those over the age of 50 and the incidence rate of the disease is expected to increase by 20% by 2025 [1,7]. CRC is a silent disease with overt symptoms not usually occurring until an advanced stage [8]. Early detection and treatment is vital in reducing the disease impact because survival decreases with increasing stage of disease at diagnosis [9]. Randomized control trials have shown that screening using the FOBT can reduce mortality from CRC by 25% [10]. A number of Canadian organizations have outlined CRC screening recommendations emphasizing FOBT at least every two years for average risk men and women between 50 to 74 years of age [1,11-14].

In Manitoba, patients may access FOBT screening through one of two routes: (1) a population-based screening program (ColonCheck) in Manitoba promotes screening through direct mailing, distribution at mammography clinics, the Mobile Breast Screening Program, publicity campaigns) but is not yet available to all Manitobans, and (2) Family physicians (FPs) which are the second access point to screening with an FOBT. The complexities of clinical practice and time constraints of the FP impact on the time available to adequately address all health concerns during the periodic health examination, especially prevention and screening [15]. Today, family physicians are responsible for caring for patients with increasingly complex multiple morbidities [16,17] and face challenges in addressing health promotion within the time constraints of clinical practice. Practitioners may also have insufficient time to access current evidence-based research findings and guidelines to support them in their CRC screening efforts [18], making knowledge translation activities between researchers and practitioners a vital component of the protocol objectives in the context of primary care research.

Tools that support family physicians in providing their patients with CRC screening information and support them in completing the test may prove useful in improving FOBT uptake among patients. In clinical practice, patients are usually given the FOBT through a laboratory requisition at their periodic health examination (PHE), provided the FOBT card from the physician’s support staff, or given it directly by their family physician and instructed to return it to the laboratory after they have completed it (unpublished observations; KC).

The first point of contact for a majority of patients seeking healthcare is with a community-based family physician. Family physicians play a key role in quality healthcare delivery, including CRC screening [19]. Manitobans depend on their family physicians to inform them of the need for FOBT testing in the prevention of CRC [8]. Physicians estimate it takes approximately four minutes to do a good job of explaining CRC and relevant screening options [20]. This represents between 27 and 40% of the total time available during the periodic health examination. In 2005, a study by Stokamer et al. demonstrated an increase in FOBT compliance from 51.3% to 65.9% using intensive one-on-one CRC education by registered nurses that took an additional 4.6 minutes beyond the time of standard CRC screening patient education (consisting of written instructions for the FOBT and verbal instruction to return the completed test within two weeks) [20]. Family physicians require supportive tools to facilitate FOBT recommendation and compliance among their patients to improve overall FOBT screening rates. Research is required to identify innovative methods of supporting family physicians in their role in CRC screening. Developing strategies aimed at supporting both the primary care provider as well as their patients has the potential to lead to substantial improvements in FOBT screening rates. Patient education about CRC and the importance of screening has been demonstrated to improve patient knowledge and compliance with FOBT [20,21]. Substantial improvements in FOBT completion rates have been demonstrated by studies that emphasized the importance of the FOBT, increased patient confidence in their ability to complete the FOBT, taught patients how to do the test, and provided time for patients to ask and receive answers to their individual questions about CRC and the FOBT [20]. Intervention strategies resulting in higher completion rates commonly involve one-on-one patient contact in clinics by registered nurses which is costly, time consuming [20], and uncommon in most community-based fee-for-service clinical practices in Manitoba. It may be more cost-effective to utilize a less expensive strategy, specifically a telephone support line managed by registered nurses. Another alternative may also involve access to a website with CRC information and FOBT assistance for patients. Although personalized emails from a physician reminding patients to undergo CRC screening and provided a link to a webpage with information about CRC did not improve FOBT compliance among patients [22], a multimedia educational computer program was demonstrated to be as effective as usual nurse counseling in educating patients and achieving adherence to FOBT screening [23].

Both patients and family physicians seem to be involved in a complex scenario resulting in sub-optimal colorectal cancer screening rates. There has been progress in patient awareness of colorectal cancer and the importance of screening [2]. A number of unique barriers to FOBT screening remain which lead to poor patient compliance [3]. In 2008, a colorectal cancer screening survey of 2,230 Manitobans aged 50 to 74 years demonstrated that only 26% had an FOBT within the previous year [3]. Factors identified by patients in the survey as contributing to low uptake among those eligible for CRC screening included: i) lack of knowledge about CRC and understanding of the significance and role of CRC screening in preventing and detecting the disease [2]; ii) lack of familiarity with the purpose of the FOBT; (iii) barriers associated with the test itself including the instructions for performing the FOBT [24,25] and iv) perception that the required collection of stool samples is an unpleasant task [26]. Additional reasons given by patients for not completing the FOBT included that: i) they didn’t think it was really needed or necessary (19%); ii) they thought the test sounded complicated (3%); iii) they didn’t really understand the test and why they should do it; iv) they did not want to handle stool (3%); and v) they meant to but didn’t think about it or forgot (3%) [3]. The survey also revealed that of those provided with an FOBT, 10% did not complete it. Among the reasons for completing an FOBT test, 79% of Manitobans surveyed said that it was included as part of a routine physical check-up or screening. Among those who did not do the test, 75% said it was because their doctor did not suggest it. This highlights the impetus and objectives of the protocol, to address the constraints of clinical practice and support family physicians in initiating CRC screening with their patients while at the same time, promoting patient understanding of the disease and the desire to take action and complete the test.

This protocol addresses the importance of promoting understanding of the FOBT among patients as well as their level of awareness, knowledge and education about CRC and screening practices. At the same time, it addresses the time constrains encountered by family physicians in adequately addressing CRC screening with their patients.

The patient decision aid used in this protocol is based on the Health Belief Model in that patient health prevention behaviors are largely determined by perceived susceptibility and seriousness of a health threat or personal risk [21], the patients’ consideration of benefits and barriers to action, including adequacy of information to cue action and self-efficacy or confidence in the ability to successfully take action [21]. Patient barriers to FOBT compliance are consistent with the Health Belief Model as they include limited accurate knowledge and understanding of CRC and screening tests for CRC, low perception of personal risk for CRC in the average-risk population, inconvenience, aversion to stool testing, lack of confidence in the ability to do the FOBT, the perception that the FOBT is time consuming, and fear of the consequences of screening [18,20].

In 2009, 66% of Canadians 45 years and older went online and represent an age group that is typically slower to adapt to and use the internet [27]. In 2010, 77.1% of Canadians had home internet access compared to 73% of Manitobans. Among those using the internet from home, approximately 75% went online every day in a typical month and 70% searched for medical or health related information online [28]. Seventy-four percent of females searched for information about health or medical conditions compared to 66.7 of men. In 2009, 71.6% of at home internet users were between 35–54 years of age compared to 69.1% of those 55–64 years, and 65.9% of those 65 years and older [29]. In 2010, 80% of individuals between the ages 45–64 used the internet compared to approximately 51% aged 65–74 and 27% aged 75 years and older. Household income quartile as well as urban versus rural community internet access are factors influencing internet use [27]. The role of the internet in assisting with and supporting positive health promotion behaviors in Manitoban’s age 50–74 years of age is currently unknown. Findings from the study outlined by this protocol will illuminate whether the internet is a possible medium for consideration as a means to support community-based family physicians in improving colorectal cancer screening of their patients.

